# 5. Objectives

## 5.1 Primary objectives and research questions

Primary objective 1: Examine effect of mHealth solutions in the form of job-aid to ASHAs during her scheduled home visit to increase coverage of selected MNCH interventions to be provided by her in tribal and rural areas of Gujarat.

Research question 1: Can mHealth solutions in the form of job-aid to ASHAs during her scheduled home visit increase coverage of following indicators compared with usual care among tribal areas of Gujarat?

There will be two primary outcomes of interest.

The first being proportion of neonates/mothers who receive at least two postnatal home visits within first week of delivery by ASHA. As most of the neonatal deaths occur during first few days of life, it is recommended that neonates should be visited three times during first week including day of delivery, third day and preferably seventh day[[35]](#footnote-36). However, most (78% according to coverage evaluation survey of UNICEF in 2009) of the deliveries in Gujarat now occur in facility where ASHAs’ role ends up being limited in presence of the facility based more qualified health workers[[36]](#footnote-37). Also, ASHAs’ visit on the day of delivery is influenced by variety of factors with limited role of the ImTeCHO intervention. Hence, we decided to focus on coverage of ASHAs’ two visits during first week after the mother/neonates returns home after discharge from the facility.

- Improve proportion of neonates/mothers who received at least two postnatal home visits within first week of delivery by ASHA from 46% to 66%.

The second primary outcome of interest will be a composite coverage index will be calculated using following formula and rationale.

Modified ASHA-centric composite coverage index (MACCI) = 0·25 × (0.33 × [Complete ASHA home visit during antenatal period +Full ANCS+SBA] + [Complete HBNC] + 0·5 × [DPT3 + EBF] + 0·33 × [Care seeking for newborn complications+ORT + ARI/febrile illness])

In which,

1. Maternal care domain

- Complete ASHA home visit during antenatal period = proportion of mothers who were visited at home by ASHA at least three times during last pregnancy including at least one visit during last trimester,
- Full ANCS = proportion of mothers with full antenatal examination (at least three antenatal examination, one Inj.TT and 100 IFA tablets)Error: Reference source not found
- SBA = proportion of mothers who delivered in a facility as most of the deliveries attended by skilled attendant are those taking place at a facility in GujaratError: Reference source not found

1. Newborn care domain

- Complete HBNC = proportion of neonates/mothers who received the recommended number of postnatal visits and at recommended times within first month of delivery by ASHAError: Reference source not found

1. Young infant care domain

- DPT3 = proportion of infants (6-8 months) who received three doses of diphtheria, pertussis, and tetanus vaccine or three doses of pentavalent vaccine
- EBF = proportion of infant (6-8 months) who were exclusively breast fed for first six months,

1. Morbidity management domain

- Care seeking for newborn complications = proportion of neonates who had complications within first month of last delivery and sought care from ASHA
- ORT = proportion of infants (6-8 months) who had diarrhea within last two weeks and received ORS from ASHA
- ARI/fever = proportion of infant (6-8 months) with ARI/fever within last two weeks and sought care from ASHA

The weight of morbidity domain will be nullified if no morbidity was found for a particular ASHA.

Improve MACCI from 36% to 51%.

Regarding the use of composite indicator, we were guided by Composite coverage index (CCI) which is now widely used to measure coverage of key MNCH interventions and strength of health-system[[37]](#footnote-38),[[38]](#footnote-39),[[39]](#footnote-40). It provides summary measure to assess continuum of care. Formula for calculating CCI is as following.

CCI= 0·25 × (FPS + 0.5 × [SBA + ANCS] + 0·25 × [2DPT3 + MSL + BCG] + 0·5 × [ORT + CPNM])Error: Reference source not found

In which FPS is family planning needs satisfied. Above interventions were selected because of its impact on mortality, measurability, availability of data, relevance with health system strength and as reflection across continuum of care. All above indicators were calculated using standard countdown 2015 definitions [[40]](#footnote-41).

For this study, a modified composite summary measure is required which can reflect (1) coverage of MNCH interventions to be provided by ASHA in India (2) scope of ImTeCHO intervention (3) relevance in India. Therefore, CCI was modified without violating basic concept of CCI. Based on evidence of effectiveness of postnatal home visits by ASHA to reduce neonatal mortality in India and national recommendations from the government, a measure of postnatal home visit was added in the modified MACCIError: Reference source not found. Also, post-natal care for newborns is a countdown 2015 indicatorError: Reference source not found. Considering high prevalence of malnutrition in India, and role of ASHA in promoting young infant feeding practices, exclusive breast feeding up to six months was included in MACCIError: Reference source not found. It is also a countdown 2015 indicatorsError: Reference source not found. Care seeking for newborn was included considering its important association with newborn mortality, role of ASHAs and ImTeCHO’s component for management complicationsError: Reference source not found,Error: Reference source not found. Management of ARI/febrile illness was added as it was done during DLHFS which is being used for this study as wellError: Reference source not found. Family planning needs satisfied (FPS) was removed as it FPS is not focus of ImTeCHO intervention. Coverage of measles was removed because the respondents for the endline survey will be limited to mothers of infants between ages of six to eight months. Also, coverage of measles and BCG vaccination is already highError: Reference source not found. Hence, formula for MACCI is designed as following:

Modified ASHA-centric composite coverage index (MACCI) = 0·25 × (0.33 × [Care Complete ASHA home visit during antenatal period +Full ANCS+SBA] + [Complete HBNC+] + 0·5 × [DPT3 + EBF] + 0·33 × [Care seeking for newborn complications+ORT + ARI/febrile illness])

Same weight was given to each of the all four main domains of interventions throughout the continuum of care which includes maternal, newborn, young infant care and care seeking for complications.

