**Table 5 Coverage of selected maternal, newborn and child interventions in Gujarat (DLHFS-3, 2007-08)**

| **Indicators** | **Total (%)** | **Rural (%)** | **Urban (%)** |
| --- | --- | --- | --- |
| Mothers who received any antenatal check-up | 71.5 | 66.4 | 88.4 |
| Mothers who had antenatal check-up in first trimester | 52.4 | 45.9 | 73.4 |
| Mothers who had three or more ANC | 56.8 | 50 | 79 |
| Mothers who had at least one tetanus toxoid injection | 68.6 | 63.1 | 86.4 |
| Mothers whose Blood Pressure (BP) taken | 51 | 44.8 | 71.3 |
| Mothers who consumed 100 IFA Tablets | 50.7 | 52.3 | 45.4 |
| Mothers who had full antenatal check-up | 19.9 | 16 | 32.8 |
| Mothers who received post-natal care within two weeks of delivery | 59.5 | 52.9 | 81.1 |
| Children under 3 years breastfed within one hour of birth | 48.3 | 47.4 | 51.6 |

Asd

**Table 6 Coverage of selected MNCH interventions in selected villages of Jhagadia block during 2014****[[14]](#footnote-15)**

| **Indicators** | **Prevalence (%)** |
| --- | --- |
| **ANC** |  |
| First antenatal examination during first trimester | 57% |
| Full antenatal examination | 19% |
| At least 4 ANC examination by ANM/doctor | 79% |
| At least 3 ANC home visit by ASHA | 65% |
| **DELIVERY** |  |
| Early initiation of breast feeding | 73% |
| **POSTPARTUM** |  |
| ASHA visited at home within 24 hours of delivery (in case of home delivery) or within 24 hours of return to home from hospital in case of hospital delivery | 32% |
| At least 5 home visit by ASHA within first month of delivery AND 2 home visit within first week (irrespective of place of delivery) | 2% |
| Mothers who received satisfactory education/counseling about caring for newborn baby from ASHA during her home visits after last delivery | 2% |
| **YOUNG CHILDREN (6-9 MONTHS)** |  |
| Exclusive breast feeding | 23% |
| Child was fed solid, semisolid or soft food at least once within last 24 hours | 74% |
| Mother knew status of child on WHO growth chart | 6% |
| **CARE SEEKING** |  |
| Sought help from ASHA for ANC complication | 54% |
| Sought help from ASHA for postnatal maternal complication | 9% |
| Sought help from ASHA for newborn complication | 27% |
| Received ORS | 43% |
| Child received ORS and ORS was supplied by ASHA | 6% |
| Sought help from ASHA for pneumonia/fever | 23% |

*3.2 Low care seeking from appropriate health personnel*

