Large number of neonates and pregnant women with complications do not seek care at health facilityError: Reference source not found,[[15]](#footnote-16),[[16]](#footnote-17),[[17]](#footnote-18) and those who are unable to go to health facility do not receive any care at homeError: Reference source not found. Only 25% of neonates and 55% of pregnant women with complications sought treatment from a health facility in Jhagadia block, Gujarat (in-service data, SEWA Rural). 61% of women sought care for any complications during antenatal period whereas only 59% of women sought care for post-delivery complications in GujaratError: Reference source not found. Only 41% of newborns with complications got treatment from a health facility in study conducted in Wardha, India[[18]](#footnote-19). Poor care seeking could be due to delay in recognition of complications at community level because of lack of knowledge about danger signs and presence various barriers for seeking careError: Reference source not found,Error: Reference source not found,[[19]](#footnote-20),[[20]](#footnote-21). Only a quarter of households in Gujarat had knowledge about danger signs among newbornsError: Reference source not found. 46% of newborns with complications did not get any care in a study conducted at WardhaError: Reference source not found. Large numbers of complicated cases who stay home do not receive any care at home due to non-availability of doctors or other qualified health personnel at homeError: Reference source not found. Though the ANM is expected to attend to complicated cases at home in case the family is unable to go to health facility, there is no system in place where ANMs and medical officers could be notified immediately about such complicated cases at home. This limits their capacity to track and attend to such cases. ASHAs, who are trained to identify and manage selected minor newborn and maternal complications, find it difficult to remember complex algorithms and management guidelinesError: Reference source not found which limits their capacity to appropriately manage complicated cases at home.

3.3 *Inadequate information and institutional capacity for monitoring and supporting maternal, newborn and child care services to be provided through ASHA.*

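### MACCI's three morbidity items count only care from the ASHA, so they cannot support the Summary's broader claim about the care that complicated cases get; the Table 9 ORS planning value also needs reconciling.

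*Protocol*

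**What the plan says.** Section 5.1 defines the morbidity domain by three items. The first, on sick newborns, is the "proportion of neonates who had complications within first month of last delivery and sought care from ASHA". The second is about diarrhoea and is restricted in the same way, to the "proportion of infants (6-8 months) who had diarrhea within last two weeks and received ORS from ASHA". The third treats respiratory illness and fever alike: among infants of that age who were ill in the past fortnight, it counts those whose families turned to the ASHA.

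They enter the index as "0·33 × [Care seeking for newborn complications+ORT + ARI/febrile illness", inside the overall factor of 0.25. The only adjustment is that "The weight of morbidity domain will be nullified if no morbidity was found for a particular ASHA".

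The ASHA focus is openly stated. The primary objective concerns services the ASHA is to provide, and the first thing the index must reflect is "coverage of MNCH interventions to be provided by ASHA in India". Section 1 (Summary) is broader: it lists the care that complicated cases receive as a primary outcome and names no provider. Section 3.2 describes the problem partly as low use of facilities: "Only 25% of neonates and 55% of pregnant women with complications sought treatment from a health facility".

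Table 6 in Section 3.1 (Jhagadia villages, 2014) separates ORS from any source, 43%, from the row "Child received ORS and ORS was supplied by ASHA", 6%. Table 9 in Section 8 plans 0.65 in control and 0.75 under intervention for ORS received from the ASHA.

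**The concern.** Care from an ANM, a PHC, a hospital or any other supplier never enters the numerator of these items. A child treated elsewhere still counts as morbidity, so the nullification rule does not remove that child. MACCI therefore cannot tell a change of provider from an increase in care, and a family that moves from no care to direct facility care leaves the score unchanged.

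The intervention makes both movements plausible. It uses counselling videos on danger signs, emergency referral of severe cases and a helpline that encourages facility care, and it also sends stock alerts that keep the ASHA's kit supplied.

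The index is also mixed within itself. A facility birth counts as covered, and the antenatal and DPT3 items name no provider, yet facility care for a sick newborn counts as uncovered. The ORT and pneumonia terms of the parent index, as printed in Section 5.1, carry no ASHA restriction either.

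At stake is what a positive MACCI result may be said to show. Read with the Summary, it would be taken as evidence that more complicated cases received care.

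**Working it through.** **Inputs.** MACCI formula and item definitions: Section 5.1. Planning values: Table 9. ORS by supplier: Table 6 in Section 3.1. Table 9 gives 10 newborn-complication cases per cluster, against 22 for the non-morbidity items, so the denominator is read as sick newborns.

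**The plan's own figure.** With 0.36 v 0.51, 22 ASHAs per cluster, ICC 0.02, 80% power and two-sided 5%, the unpooled two-proportion formula gives 167.5 per arm. The design effect is 1 + 21 × 0.02 = 1.42, and 167.5 × 1.42 / 22 = 10.81. This rounds to the stated 11 clusters, before any allowance for a lost cluster. So 0.36 and 0.51 drive the sample size.

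**MACCI rebuilt from the Table 9 rows.**

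- Control: 0.25 × (0.33 × [0.65 + 0.45 + 0.85] + 0.05 + 0.5 × [0.67 + 0.50] + 0.33 × [0.27 + 0.65 + 0.27]) = 0.25 × (0.6435 + 0.05 + 0.585 + 0.3927) = 0.418
- Intervention: 0.25 × (0.33 × [0.90 + 0.60 + 0.90] + 0.30 + 0.5 × [0.67 + 0.70] + 0.33 × [0.50 + 0.75 + 0.50]) = 0.25 × (0.792 + 0.30 + 0.685 + 0.5775) = 0.589

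The difference is 0.171, against the stated 0.15. If only the control ORS value is changed from 0.65 to 0.06, the control morbidity term becomes 0.33 × 0.60 = 0.198 and control MACCI becomes 0.369, close to the stated 0.36.

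**Weight of one item.** 0.25 × 0.33 = 0.0825, or 8.25 MACCI points.

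**Change of ORS supplier with no extra child treated.**

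- Planned rise, 0.65 to 0.75, if all substitution: 0.0825 × 10 = 0.8 points
- Extreme case, 6% to 43%, with total ORS use fixed at 43%: 0.0825 × 37 = 3.1 points

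**Sick newborns going straight to hospital instead of to the ASHA.** Every child still receives care and the other items are held fixed. The 10 and 20 are assumed; 27 is the whole planned control value.

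| Displaced per 100 sick newborns | Change in MACCI (points) |
| --- | --- |
| 10 | −0.8 |
| 20 | −1.7 |
| 27 | −2.2 |

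The change is zero for a newborn who moves from no care to direct hospital care. It is also zero for one taken first to the ASHA and then referred, who still counts as covered.

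**Ceiling from the plan.** The domain's planned gain is 0.0825 × (0.23 + 0.10 + 0.23) = 0.0462, or 4.6 points, which is 27% of 0.171. This bounds how much of the gain implied by Table 9 could be change of provider. It is not an estimate.

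**The case against.** The strongest reply is that the restriction is deliberate and fits the estimand. The primary objective is about what the ASHA provides, the index is named for her, ORS belongs in her expected kit, and facility referral has its own place in secondary objective 1. MACCI is also the stratification variable and the basis of the 11 clusters, so redefining it would disturb the randomization and the sample size. All of this stands, and it rules out replacing the primary index.

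A reader might infer three stronger points that the documents do not support.

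- **The index falls whenever facility care rises.** It falls only when facility care displaces contact with the ASHA. The main referral route runs through her, and no section quantifies bypass.
- **The newborn item rests on its link with mortality alone, so the source of care cannot matter.** Section 5.1 also gives the role of the ASHA and the intervention's own component for complications as reasons.
- **The 0.65 shows that two definitions of ORS coverage were mixed.** It matches neither 6% nor 43%, and its cited source is not legible in the text at hand. It is an unreconciled planning value and no more can be said.

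Two limits also stand. The Section 3.1 figures come from the comparison area of an evaluation in Jhagadia, not from the trial blocks. Appendix 1, which lists the secondary indicators, is not shown and may already hold provider-neutral measures. Neither removes the gap between the Summary's wording and what MACCI scores.

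**Conclusion.** The point holds as one of interpretation, and the ASHA-only definition can stay. As scored, the morbidity domain supports conclusions about ASHA-delivered care and does not support the Summary's unrestricted statement about complicated cases. The size is modest: up to 0.8 points for the planned ORS rise and 3.1 in the extreme substitution case, against a 15-point target. These figures assume the formula as printed, the other items fixed and no nullified domain.

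The Table 9 discrepancy is separate and definite. The ORS row exceeds even the any-source figure in Section 3.1, and the component rows do not produce the stated 0.36 and 0.51.

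**What to change.** 1. **Section 5.1:** keep MACCI as defined. Add a named companion index that scores each of the three morbidity items as covered if the care or ORS came from the ASHA, an ANM, a PHC or another qualified provider, computed from the same household survey and reported beside MACCI.
2. **Section 1 and the planned conclusions:** say that MACCI's morbidity domain measures ASHA-delivered care, and draw any wider claim about complicated cases from the companion index or secondary objective 1.
3. **Table 9:** reconcile the ORS row (0.65) with the Section 3.1 coverage table (6% from the ASHA, 43% from any source), give the source, and restate the MACCI planning values so that they follow from the rows.

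The first two changes cost one more computed index and some wording, and leave stratification and the cluster count untouched. They assume that the questionnaire records source of care. The split of ORS by supplier in Section 3.1 suggests that it does, but Appendix 2 is not shown. The third may alter the sample-size inputs; Section 8 already foresees a revision after the baseline survey. The downside is that the provider-neutral domain may show a smaller gain, because care from any source starts higher.

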## 5.2 Secondary objectives and research questions

Secondary objective 1: Examine effect of ImTeCHO intervention in the form of job aid to ASHA and ANM to increase coverage of care among complicated maternal, newborn and child cases by facilitating referral to a health facility and managing at home for those cases that unable to get referred in tribal areas of Gujarat.

Secondary research question 1: Can ImTeCHO intervention in the form of job-aid to ASHAs and ANM increase coverage of care among complicated maternal, newborn and child cases in tribal areas of Gujarat?

Complete list of set of indicators for secondary objective 1 can be found in Appendix 1.

Secondary Objective 2: Examine effect of ImTeCHO intervention in the form of a job aid to medical officers and PHC staff to improve support and supervision of ASHAs.

Secondary research question 2: Can ImTeCHO intervention in the form of a job aid to medical officers and PHC staff improve support and supervision of ASHAs?

- Proportion of ASHAs whose performance was reviewed by mHealth facilitator (more about mHealth facilitator in section 10.2) over a phone call per month
- Proportion and number of ASHAs who were contacted by mHealth facilitator (mostly through phone) every month for non-adherence to intervention
- Proportion of ASHAs who were visited in field by ImTeCHO facilitator for quality improvement
- Proportion of PHC meetings when [data from] ImTeCHO was used at least once for supervision by PHC staff
- Medical officer’s login and task completion rate
- Average number of phone call by SEWA Rural’s ImTeCHO facilitator per ASHA per month towards providing support
- Proportion of beneficiaries with high risk complications who received guidance from SEWA Rural’s helpline
- Average number of phone call by SEWA Rural’s helpline per ASHA per month towards providing guidance for morbidity management
- Average number of motivational announcements sent by SEWA Rural to ASHAs per month
- Average amount of extra incentives paid by SEWA Rural per ASHA per month

Secondary objective 3: Examine process indicators to understand processes and level of adherence to intervention.

Selected process indicators are listed below and complete list of process indicators are given in Appendix 1. The process indicators will be measured for intervention area only. Please refer to Figure 2 and 2 to see conceptual frameworks which were used to identify process indicators.

| **Sr no** | **Process indicators** |
| --- | --- |
| *Intervention 1: Mobile as a job-aid to ASHAs during her scheduled home visit to increase coverage of selected MNCH interventions* | |
| 1.1 | ASHA attendance rate (login rate)* |
| 1.2 | Number of home visit forms filled using mobile phones against expected (Task completion rate)* |
| 1.3 | Number of pregnancy registration forms filled using mobile phones against expected number of registration |
| 1.4 | Time taken (Mean, median, range) to complete mobile based home visit forms (Rationale: indirect measure of quality of interview) |
| 1.5 | Proportion of live and still births reported on the day of outcome |
| 1.6 | Proportion of beneficiaries who attended VHND against expected number (VHND attendance rate) |
| 1.7 | Line listing of beneficiaries with various due services (eg. ANC examination, HBNC, Vaccination, growth monitoring, ) |
| *Intervention 2: Mobile phone as job aid to ASHA and ANM to increase coverage of care among complicated maternal, newborn and child cases by facilitating referral to a health facility and managing at home for those cases that refuse to get referred* | |
| 2.1 | Number of complicated maternal (severe anaemia), newborn (LBW) and child (severe underweight) cases identified against expected |
| *Intervention 3: mHealth solutions in form a web interface to provide tools and timely information to PHC staff for monitoring and supporting MNCH program* | |
| 3.1 | Proportion of days when web interface was reviewed by medical officer (Attendance of medical officer with use of web interface) |
| 3.2 | Stock-out rate (Proportion of times when a drug or equipment was not available when required. Eg. Non-availability of antibiotics in case of of child with pneumonia) |
| 3.3 | Timeliness of incentive payment to ASHA |

Secondary objective 4: Examine effect of ImTeCHO intervention in the form of job-aid to ASHAs, ANMs, medical officers and PHC staff to increase coverage of selected MNCH interventions and care to be provided for complicated maternal, newborn and child cases in tribal areas of Gujarat.

Complete list of set of indicators for secondary objective 4 can be found in Appendix 1.

